#### 2.3.1. Rationale for dose selection.

Preclinical studies using NPC mouse models used an Efavirenz dose 300 times smaller than the 1 used in HIV patients.^[14]^ Although very small, the dose used has been proven to activate CYP46 and efficiently promoted the recycling of cholesterol in the brains of normal mice.^[14]^

However, extrapolating preclinical doses to a clinical setting is challenging. The significant differences in body size, brain size, and the blood-brain barrier must be considered, among other things. Also, administering humans with a dose as low as the 1 administered in mice would risk not having the desired effect.

Notably, 1 clinical trial (NCT03706885, ClinicalTrials.gov) is currently being conducted in patients with Alzheimer’s dementia using oral doses of EFV of 50 and 200 mg/d to activate CYP46 in the brain.

In light of all that, the study team has selected a dose of 25 mg/d of EFV, considering that the desired effect should be observed with this dose – a dose 24 times smaller than the recommended antiretroviral dose for HIV patients (600 mg/d). Given that increases in plasma 24-OH-Cholesterol concentrations (≥1.5 times the pre-EFV baseline values) have been observed in the preclinical studies, we will perform successive blood tests (every 3 months). If no 24-OH-Cholesterol increases ≥ 1.5 times the pre-EFV baseline values are observed, we shall consider increasing the dose to up to 200 mg/d.

### 2.4. Criteria for discontinuing or modifying allocated interventions

As mentioned before, all enrolled patients will receive EFV + SoC. The EFV will be discontinued if the investigator deems that it poses an unacceptable risk to the patient; the patient withdraws his consent; there is a significant violation of the study protocol; there is a loss to follow-up; or in case a study participant becomes pregnant.

### 2.5. Strategies to improve adherence to intervention

In addition to collecting and reviewing empty medication boxes, patients will be provided with a “Patient’s diary” for better controlling treatment adherence.

### 2.6. Relevant concomitant care permitted or prohibited during the trial

As mentioned in the exclusion criteria, the following concomitant medications are prohibited during the trial:

•CYP3A4 inhibitors, including, but not limited to terfenadine, astemizole, cisapride, midazolam, triazolam, pimozide, bepridil, or ergot alkaloids (e.g., ergotamine, dihydroergotamine, ergonovine, and methylergonovine). Substrates that compete with EFV for CYP3A4-binding could decrease its metabolism and induce serious and/or life-threatening adverse reactions (e.g., arrhythmias, prolonged sedation, or respiratory depression).•Elbasvir and Grazoprevir, because EFV has the potential to significantly decrease plasma concentrations of both drugs.•Herbal medicinal products containing St. John’s Wort (*Hypericum perforatum*) due to the risk of decreasing plasma concentrations and the clinical effects of EFV.•Drugs known to prolong the QTc interval, including, but not limited to class IA and class III antiarrhythmics; neuroleptics; antidepressant agents; certain antibiotics (e.g., macrolides, fluoroquinolones, and imidazole and triazole antifungal agents); certain non-sedating antihistamines (terfenadine, astemizole); cisapride; flecainide; certain antimalarials; and methadone.

### 2.7. Outcomes:

Primary and secondary outcomes are summarized in Table 2.

**Table 2 T2:** Summarized outcome measures.

Primary outcome measure	
Change (not deterioration) in cognitive performance at 52 wks of starting treatment with EFV, assessed by:	
CDR-SoB score.	
FCSRT score (to evaluate verbal memory).	
The executive functions as per the following:	
a)a-BT scores in the digit span subtest.	
b)a-BT scores in the mental control subtest.	
c)Scores in verbal fluency subtest: semantic and phonemic tasks.	
d)TMT A and B scores	
e)SCWT scores.	
Secondary outcome measures	
**Clinical**	Neurological: Changes at 52 wks of starting treatment with EFV relative to baseline in:
	SARA score
	EAT-10 score.
	PDS score
	• Neuropsychological (protocol used in clinical practice): In general, the scaled score will be determined for the following questionnaires/scales:
	CDR-SoB^*^ score.
	*Note: It offers a specific score from 0 to 18, the higher the score the greater the severity.
	FCSRT score
	a-BT assessment in the following domains:
	◦Orientation, digit span, automatized sequences (e.g., counting to 20, d of the wk, mo of the yr), comprehension of verbal commands, and comprehension of complex verbal material (i.e., yes-or-no answers to BDAE-based questions) subtests’ scores.
	◦Bilateral gesture-based limb praxis test
	◦Visual memory (i.e., figures)
	◦Reading, repeating, and writing
	◦Mental and written arithmetic
	◦Reciprocal coordination
	◦Unilateral alternating sequences subtest (e.g., serial hand tests, such as fist-palm-side, tapping).
	◦Constructional praxis (drawing copy).
	Verbal Fluency score: Semantic and phonemic tasks
	TMT A and B scores
	SCWT score
	WAIS-III/WAIS IV
	BNT, Naming and Semantic Knowledge subtests’ scores
	JLO Test score.
	DEX questionnaire score.
	NPI score.
	AES score.
	BDI score.
	C-SSRS score.
**Biological**	• Brain ^18^FDG PET–Scan: Quantification of cerebellar, cortical, and thalamic metabolism.
	• Brain MRI: Cortical, white matter, basal ganglia, and cerebellar structures volumetric analysis.
	• Abdominal ultrasound: Spleen size (cm).
	• Oculography: initial speed, amplitude, and execution speed of vertical and horizontal saccades
	• Plasma Oxysterols levels
	• Plasma Lyso-SM-509 level
	• Plasma 24-OH-Cholesterol level
	• Cerebrospinal Fluid (CSF) Beta-Amyloid, Tau, and phosphorylated Tau levels
**Safety**	• Number of adverse events (AEs) according to seriousness, severity, and relationship with EFV.
	• Changes in the liver function panel

8 FDG PET—scan = ^18^Fluorodeoxyglucose Positron emission tomography scan, a-BT = abbreviated Barcelona test, AES = apathy evaluation scale, BDI = Beck’s depression inventory, BNT = Boston naming test, CDR-SoB = clinical dementia rating scale-sum of boxes, C-SSRS = Columbia suicide severity rating scale, DEX = dysexecutive questionnaire, EAT-10 = the eating assessment tool score, EFV = efavirenz, FCSRT = free and cued selective reminding test, JLO = judgement of line orientation test, MRI = magnetic resonance imaging, NPC = Niemann-Pick disease type C, NPI = neuropsychiatric inventory, PDS = Pineda disability scale, SARA = scale for the assessment and rating of ataxia, STROOP = Stroop color and word test, TMT = trail making test, WAIS = Wechsler adult intelligence scale.

A *deterioration in the CDR-SoB* is defined as an increase of ≥ 2 points at 52 weeks of starting treatment with EFV relative to baseline.

A *deterioration in verbal memory* is defined as a decrease of ≥ 1 in the standard deviation (SD) at 52 weeks of starting treatment with EFV relative to baseline.

A *deterioration in the executive function* is defined as a decrease of ≥ 1 in the SD (in at least 2 of the 5 tests performed) at 52 weeks of starting treatment with EFV relative to baseline.

A patient will be considered a responder (no decay in cognitive performance) if there is no deterioration in at least 2 of the 3 assessed items at 52 weeks of starting treatment with EFV relative to baseline.

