•Co-administration with elbasvir and grazoprevir due to the potential of EFV to significantly decrease plasma concentrations of both drugs.•Use of herbal medicinal products containing St. John’s Wort (*Hypericum perforatum*) due to the risk of decreasing the plasma concentrations and the clinical effects of EFV.•Family history of sudden death or congenital prolongation of the QTc interval or any other clinical condition known to prolong the QTc interval.•Family history of symptomatic cardiac arrhythmias, clinically relevant bradycardia, or congestive heart failure associated with a reduced left ventricular ejection fraction.•Severe disturbances of electrolyte balance, such as hypokalemia or hypomagnesemia.•Concomitant treatment with drugs known to prolong the QTc interval, such as class IA and class III antiarrhythmics; neuroleptics; antidepressant drugs; certain antibiotics (i.e., macrolides, fluoroquinolones); imidazole and triazole antifungal agents; certain non-sedating antihistamines (i.e., terfenadine, astemizole); cisapride; flecainide; certain antimalarials; and methadone.

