### 2.19. Adverse event reporting and harms

Given that EFV is an authorized medicinal product, the SmPC will be used as the Reference Safety Information.

The investigators will systematically monitor and collect the AEs from the moment of signing the written informed consent to the patient’s last follow-up visit. AEs will be recorded in the patient’s medical record, stating the causality assessment for EFV. AEs related to the EFV will be collected through the eCRF whenever they are serious (SAEs) or AEs of special interest.

The investigators must provide a thorough description of the event, including start and end dates, an intensity assessment (mild, moderate, or severe), measures taken to mitigate it (e.g., none, EFV withdrawal, the medication used to treat the AE), and a causality assessment for EFV.

Any AE or clinically relevant lab abnormality will be followed until satisfactory resolution, stabilization, or until clinical judgment indicates it has an alternative cause and no further assessment is needed.

The investigator must notify the contracted contract research organization of any SAE (including death from any cause) in less than 24 hour after becoming aware of it, regardless of its relationship with EFV. This will be done by sending a specific notification form by fax or email.

Any suspected unexpected serious adverse reaction (i.e., those not reported in the Reference Safety Information) will be of expedited reporting as per the current Spanish (Royal Decree 1090/2015) and European legislation (Regulation EU 536/2014).

For the purpose of this trial, we consider as AEs of special interests laboratory abnormalities in plasma liver enzymes (aspartate aminotransferase and alanine aminotransferase > 2× upper limits of normal).

In the event of a pregnancy during the study, the EFV will be immediately withdrawn. The investigator must notify the sponsor within 24 hours of becoming aware of the event. Appropriate medical assistance will be offered to the patient. These patients will be asked to sign a specific written informed consent allowing the investigators to collect pregnancy-related data. The patient will be followed until the delivery date; if the outcome meets SAE criteria, the investigators will follow the procedures explained before for SAE notification.

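### The protocol guards against QTc and arrhythmia risk and schedules four on-treatment EKGs per patient, but lists no EKG or QTc safety outcome, and a non-serious QTc prolongation has no stated adverse-event route into the eCRF

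*Protocol article*

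**What the plan says.** **Eligibility and prohibited drugs.** Section 2.2.2 contains a run of cardiac exclusions: "Family history of sudden death or congenital prolongation of the QTc interval or any other clinical condition known to prolong the QTc interval"; "Family history of symptomatic cardiac arrhythmias, clinically relevant bradycardia, or congestive heart failure"; "Severe disturbances of electrolyte balance, such as hypokalemia or hypomagnesemia"; and "Concomitant treatment with drugs known to prolong the QTc interval". The note on the CYP3A4 substrates in the same section gives cardiac arrhythmia as one of the harms to be avoided. Section 2.6 keeps both groups of drugs prohibited during the trial.

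**Measurement.** Table 3 (section 2.7.1) ticks the EKG row at Visits 1, 3, 4, 5 and 6, that is, at baseline and at weeks 13, 26, 39 and 52.

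**Outcomes.** The safety part of Table 2 (section 2.7) has two entries: "Number of adverse events (AEs) according to seriousness, severity, and relationship with EFV" and "Changes in the liver function panel".

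**Special interest and capture.** In section 2.19, "we consider as AEs of special interests laboratory abnormalities in plasma liver enzymes" (AST and ALT above twice the upper limit of normal) is the whole definition. The same section says that adverse events go into the medical record, and that those related to efavirenz are collected through the eCRF when they are serious or of special interest.

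**Analysis.** Section 2.15 plans a descriptive analysis of adverse events. No section defines a QTc variable, a correction formula or a change from baseline.

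**The concern.** The protocol treats liver and cardiac risk unevenly. Liver risk has exclusions, a safety outcome and an event of special interest. Cardiac risk has exclusions, drug prohibitions and repeated EKGs, but neither of the last two. No reason for the difference is given.

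The special-interest list matters because of the capture rule in section 2.19. A lengthened QTc found on a scheduled EKG in a patient without symptoms will often be non-serious, and it is not a liver enzyme abnormality. If the investigator records it as an adverse event, the medical record is its only stated destination. It could then be missing from the adverse event counts in Table 2.

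Safety is part of the primary objective (Table 1). Sections 2.3 and 2.3.1 also allow the dose to rise from 25 mg/d to as much as 200 mg/d in patients without the required 24-OH-cholesterol response. The trial could therefore finish without a stated summary of how the QTc moved on treatment, either overall or by dose.

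**Working it through.** The protocol gives no figure on this point to reproduce, and section 2.8 says that no formal sample size calculation was done. The check is a count and a side-by-side reading, followed by a look at what 14 patients could show.

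**1. EKGs scheduled (Table 3).** There are 5 ticks in 7 visit columns: 1 at baseline (Visit 1) and 4 on treatment (Visits 3 to 6). With the 14 expected patients (section 2.8), all completing, 4 × 14 = 56 on-treatment recordings. This is an upper limit, since any dropout lowers it.

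**2. Cardiac entries where results are used.**

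| Place | Entries | Cardiac entries |
|---|---|---|
| Table 2, safety outcomes | 2 (adverse event counts, liver panel) | 0 |
| Section 2.19, events of special interest | 1 (AST/ALT) | 0 |
| Section 2.15, safety analysis | adverse events only | none named |

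**3. Path of a cardiac finding under section 2.19.**
- Serious arrhythmia: notified within 24 hours whatever its cause. If related to efavirenz, it also meets the seriousness condition for the eCRF.
- Non-serious QTc prolongation recorded as an adverse event: not serious and not of special interest, so it meets neither condition and no adverse-event route into the eCRF is stated.
- Numeric QTc change that nobody records as an adverse event: could enter as visit data, but no outcome or analysis refers to it.

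**4. Timing relative to dose.** In Table 3 the 24-OH-cholesterol tests fall at the same visits as the EKGs (1, 3, 4, 5 and 6). A patient whose dose is raised after one of these tests already has an EKG on the lower dose, and has one on the higher dose if a later visit remains. The ratio of the two doses is 200/25 = 8.

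**5. What 14 patients could show.**
- Mean QTc change: the 95% CI half-width is t(0.975, 13) × SD/√14 = 2.160 × SD/3.742 = 0.577 × SD. The protocol gives no SD. For assumed SDs of 10, 15 and 20 ms the half-width is 5.8, 8.7 and 11.5 ms.
- No QTc event in 14 patients: the upper 95% bound on the event rate is 1 − 0.05^(1/14) = 19.3% (one-sided) or 1 − 0.025^(1/14) = 23.2% (two-sided).
- Chance of seeing at least one event, 1 − (1 − p)^14: 51% if p = 5%, and 77% if p = 10%.
- Dose-escalated subset: its size is unknown. If 5 patients were escalated (an illustration only), the half-width is 2.776 × SD/√5 = 1.24 × SD, or 18.6 to 24.8 ms for an SD of 15 to 20 ms.

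**The case against.** The strongest defence is that the EKGs are not idle. Section 2.7.1 says that everything in Table 3 is gathered, section 2.11 sends data from study visits to the eCRF, and section 2.13 includes clinical data among its contents. The safety committee (section 2.17.1) reviews the safety data available at each visit. Adverse events are recorded at all seven visits and analysed descriptively, and serious ones are notified promptly. A summary table and a correction formula are often left to the analysis plan, and Table 2 is by its own title a summary.

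Much of this stands. A reader might infer that the EKGs are taken and never used, or that the trial would say nothing about cardiac safety. The documents do not support either inference: committee review is a use, the Visit 1 EKG plausibly serves screening, and serious arrhythmias would be reported. A reader might also infer that QTc prolongation is the leading risk of efavirenz in this plan. No section ranks the risks. The arrhythmia mentioned in sections 2.2.2 and 2.6 with the CYP3A4 substrates is tied to drug interactions, and liver and psychiatric conditions drive exclusions too. Nor can it be claimed that the existing EKGs would settle a dose question, because the precision for all 14 patients does not carry over to a smaller escalated group.

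The defence does not reach two things. The protocol states its safety outcomes and its special-interest definition, and both name the liver and nothing cardiac. The capture rule in section 2.19 affects every non-serious event, not only cardiac ones, but for cardiac events it means that the adverse event count cannot be relied on to stand in for the missing QTc outcome. An analysis plan could add a table, but it would not ordinarily change which events the protocol sends to the eCRF.

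**Conclusion.** The point holds as a limited gap in safety outcomes and event capture. The protocol restricts entry and concomitant drugs because of QTc and arrhythmia risk and schedules four on-treatment EKGs per patient (up to 56 in all). Yet no EKG or QTc measure is among its two safety outcomes, and its one class of special-interest event is hepatic. A non-serious QTc prolongation has no stated adverse-event route into the dataset or the reported counts.

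This conclusion rests on reading section 2.19 as it is worded and on 14 patients completing all visits. The precision figures rest on assumed SDs. Whatever is added would be descriptive at this sample size, and less precise again for any dose-escalated patients. It is a cheap improvement worth making, because safety is part of the primary objective. It does not invalidate the design.

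**What to change.** 1. **Table 2 (Safety).** Add a descriptive change from baseline in QTc at weeks 13, 26, 39 and 52, using one named correction formula. Add the number of patients with a newly abnormal QTc, by a definition that the sponsor fixes in advance. Tabulate both by the efavirenz dose taken at the time of the EKG.
2. **Section 2.19.** Add QTc prolongation and arrhythmia to the events of special interest, so that non-serious events reach the eCRF and the adverse event counts.
3. **Reporting.** State that the results are descriptive and that any by-dose figures rest on few patients.

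No clinical threshold or management rule is proposed here, and action on an abnormal EKG stays with the investigator. The cost is a few lines of protocol wording, one eCRF field, one descriptive table and a few more special-interest reports. No additional test is needed, because the EKGs are already scheduled.

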### 1.3. Objectives

The primary, secondary, and safety objectives are summarized in Table 1.

**Table 1 T1:** Summarized study objectives.

Primary Objective	
•To evaluate the efficacy* and safety of EFV at an oral dose of 25 mg/d, in addition to standard treatment, in patients diagnosed with adult or late juvenile-onset NPC with cognitive impairment.	
*Note: Given that adult or late juvenile-onset NPC is rare and causes progressive cognitive impairment, treatment with EFV will be considered effective if it “slows down or stops cognitive impairment in patients diagnosed with adult or late juvenile-onset NPC with cognitive impairment.” Meaning, it is hoped that after 1 year of treatment, these patients remain at the baseline with respect to cognitive impairment.	
Secondary objectives	
**Clinical**	• Neurological: To evaluate the change in the following questionnaires/scales:
	SARA
	EAT-10 score.
	PDS
	• Neuropsychological (protocol used in clinical practice): To evaluate the change in the following questionnaires/scales:
	CDR-SoB
	Verbal memory: FCSRT
	a-BT
	Verbal fluency: Semantic and phonetic cues
	TMT A and B
	STROOP
	WAIS and the block design, symbol search and vocabulary subtests (WAIS-III/WAIS-IV)
	BNT, and the Naming and Semantic Knowledge subtests
	JLO
	DEX
	NPI
	AES
	BDI
	C-SSRS
**Biological**	• To evaluate the change in functional and imaging biomarkers related to NPC:
	^18^FDG PET—scan
	Brain MRI
	Abdominal ultrasound
	Oculography
	• Evaluate the change in biochemical biomarkers related to NPC:
	Oxysterols
	Lyso-SM-509
	24-OH-Cholesterol
	Beta-Amyloid, Tau, and phosphorylated Tau
**Safety**	• To evaluate the safety of EFV in patients diagnosed with adult or late juvenile-onset NPC with cognitive impairment.

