### 2.10. Assignment of interventions

#### 2.10.1. Allocation: Sequence generation, concealment mechanism, implementation, and blinding (Masking).

Not applicable. This is a single-arm clinical trial; thus, all enrolled patients will receive the study treatment.

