### 2.14. Statistical methods for analyzing primary and secondary outcomes

We will perform a descriptive analysis of the enrolled patients’ baseline sociodemographic and clinical data as a whole and by study groups.

The primary outcome measure will be evaluated by an analysis of covariance (ANCOVA). Cognitive performance (assessed by the previously described neuropsychological test battery at 52 weeks) will be the dependent variable, and the independent variables will be the study group and the cognitive performance assessed by the CDR-SoB at the baseline visit. Tables will be presented with model coefficients and their 95% confidence intervals (95% CI). Additionally, the effect size will be measured by presenting the marginal means per study group and their standardized difference along with their 95% CI.

Given the exploratory nature of the clinical and biological secondary outcome measures, we will use the same statistical technique outlined for the primary outcome measure. However, either generalized models or non-parametric statistics will be used depending on the distribution of the dependent variable.

R version 3.6 or higher will be used to perform the statistical analysis.

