## 3. Discussion

NPC is a complex orphan disease, consisting of an unmet medical need for patients suffering from it. Although there are over 20 ongoing studies on NPC registered in the ClinicalTrials.gov database, conducting clinical trials for assessing new therapeutic options can be quite challenging, given the disease’s low prevalence. Different therapeutic approaches are under study (e.g., Miglustat, Arimoclomol, N-Acetyl-L-Leucine), but, to the best of our knowledge, this is the first clinical trial studying the effects of EFV in adult- and late-juvenile-onset NPC.

As mentioned before, neuronal cholesterol metabolism is key for LTP, which is a major event for synaptic plasticity. The enzyme CYP46A1 hydroxylates the cholesterol and mediates the main pathway for its degradation in the brain.^[9,10]^ Given that NPC1 binds cholesterol and participates in its intracellular mobilization, we hypothesized that NPC1 would have a synapse-specific role in redistributing cholesterol and mobilizing CYP46A1 to the synaptic membrane required for LTP. We believe that the capacity of EFV to activate the CYP46A1 could compensate for NPC1 deficiency and correct synaptic changes, therefore compensating cognitive and psychiatric alterations in patients with NPC. This hypothesis is supported by preclinical data^[12,14]^ suggesting that low-dose EFV may be a promising alternative for NPC patients.

On the other hand, this study has limitations. First, the already mentioned small sample size due to the disease’s low prevalence. Therefore, interpreting the results may be tough, given that we cannot safely exclude that a given outcome happened by chance. Second, it has a single-arm design (absence of a control group). Although justifiable by the natural history of the disease, the unexpectedness of spontaneous improvement, and the lack of expected placebo effects, this type of design has idiosyncratic limitations since it could be argued that responders would have responded equally if treated only with SoC. Furthermore, the absence of a frame of reference for comparison could also make the results hard to interpret.

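### The planned primary ANCOVA does not use the responder rule that section 2.7 defines, and in a single-arm trial its study-group effect cannot be estimated

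*Protocol article*

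**What the plan says.** **Objective.** The note to Table 1 (section 1.3) calls EFV effective if it slows or stops cognitive impairment, and adds that "it is hoped that after 1 year of treatment, these patients remain at the baseline with respect to cognitive impairment".

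**Outcome.** Table 2 (section 2.7) gives the primary outcome as "Change (not deterioration) in cognitive performance at 52 wks of starting treatment with EFV, assessed by" CDR-SoB, FCSRT and a set of executive-function tests. The text below the table defines deterioration for each of three items: CDR-SoB, verbal memory and executive function. It then combines them: "A patient will be considered a responder (no decay in cognitive performance) if there is no deterioration in at least 2 of the 3" items assessed.

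**Analysis.** Section 2.14 states: "The primary outcome measure will be evaluated by an analysis of covariance (ANCOVA"). The dependent variable is cognitive performance on the battery at week 52, and "the independent variables will be the study group and the cognitive performance assessed by the CDR-SoB at the baseline visit". It continues that "the effect size will be measured by presenting the marginal means per study group and their standardized difference along with their 95% CI". Responders are not mentioned in that section.

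**Design.** Section 2.10.1: "This is a single-arm clinical trial; thus, all enrolled patients will receive the study treatment". Section 2.8 expects 14 patients and says that no formal sample size calculation was done.

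**Limitation.** Section 3 concedes that "it could be argued that responders would have responded equally if treated only with SoC", and that there is no frame of reference for comparison.

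**The concern.** The outcome section asks a yes/no question of each patient: did cognition hold over the year? The analysis section answers a different question, a comparison of mean week-52 scores between study groups, and the trial has only one group. If the plan is followed as written, the responder rule is never analysed and the effect measure that section 2.14 promises does not exist. The analyst would have to choose the primary analysis after the data are in, when the choice could be influenced by the results.

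This is not detail left to an analysis plan that is not shown. The article does fix a primary analysis, and what it fixes matches neither the outcome definition nor the design.

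**Working it through.** **Inputs.** From the article: one arm (section 2.10.1), n = 14 (section 2.8), the model terms (section 2.14) and the 2-of-3 rule (section 2.7). The article gives no alpha, power, null rate or target rate, so there is no planned figure to reproduce. The untreated deterioration rates used below are assumptions.

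**Step 1: can the ANCOVA be fitted as described?** Write the model as

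Y(week 52) = b0 + b1 × group + b2 × baseline CDR-SoB + error.

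In a single arm, group takes the same value for all 14 patients, so its column equals the intercept column. The design matrix has 3 columns and rank 2. Only the sum b0 + b1 can be estimated, not b1. It follows that:
- the study-group coefficient and its confidence interval cannot be estimated;
- the standardized difference between groups cannot be estimated;
- the marginal means per group reduce to one mean, which at the average baseline is simply the observed week-52 mean.

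What is left is a regression of the week-52 score on baseline CDR-SoB. For CDR-SoB itself, a mean change could be recovered by subtracting the baseline mean. For the other scores, the patient's own baseline on that score is not in the model, so change from baseline is not estimated. In no case is a responder counted.

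**Step 2: what would the responder proportion show at n = 14?** Exact (Clopper-Pearson) 95% intervals:

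| Responders | Proportion | 95% CI |
|---|---|---|
| 10/14 | 71% | 42–92% |
| 12/14 | 86% | 57–98% |
| 14/14 | 100% | 77–100% |

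For 14/14 the lower limit is 0.025^(1/14) = 0.768.

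**Step 3: how many untreated patients would meet the rule?** Let p be the chance that one item deteriorates within a year without the drug, equal for the three items. A patient is a responder if at most one item deteriorates.
- Items independent: P = (1 − p)^3 + 3p(1 − p)^2.
- Items moving fully together: P = 1 − p.

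| p (assumed) | Independent | Fully together |
|---|---|---|
| 0.2 | 0.896 | 0.80 |
| 0.3 | 0.784 | 0.70 |
| 0.4 | 0.648 | 0.60 |
| 0.5 | 0.500 | 0.50 |

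In these two cases, 50–90% would be responders with no drug effect. They are reference cases, not bounds on every possible dependence.

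**Step 4: does the reference rate matter?** Take 12/14 responders. The exact probability of 12 or more is 0.0065 if the untreated rate is 50%, 0.040 if it is 60% and 0.161 if it is 70%. The same result looks strong or unremarkable depending on a rate that the article does not give.

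**The case against.** **Table 2 never names a proportion of responders as the primary endpoint.** This is true, and treating the responder as the endpoint is a reading. But it is the only rule in the article that joins the three items into one answer per patient. The mismatch also does not depend on that label, because the group ANCOVA does not assess non-deterioration either.

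**Study group might mean something other than treatment arm,** for example patients who accept lumbar puncture. The article defines no such groups for the analysis. A contrast between subgroups who all take EFV could be estimated, but would not say whether EFV slows decline.

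**The limits are disclosed.** Section 3 acknowledges chance, the lack of a control and the lack of a reference, and asks for phase III trials. That stands, and it weakens any prediction that a high rate will be presented as proof. It does not repair section 2.14.

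Several stronger readings are tempting, and the article does not support them:
- *Nine competing primary tests with a 37% chance of a false positive* (1 − 0.95^9 = 0.370). Section 2.14 does not specify nine models and states no alpha or test. Section 2.7 groups the scores into three items. The 37% needs independence, which is doubtful for cognitive scores from the same patients. The group tests could not be run anyway.
- *The rule is too lenient.* A patient with a large CDR-SoB worsening alone would count as a responder, which sits awkwardly with remaining at baseline. But the objective also allows slowing, and tolerating decline in one item fits that.
- *A success threshold is missing.* A threshold is not mandatory in a small exploratory phase II trial and could sit in an analysis plan that is not shown.
- *Even 14/14 could not exclude the untreated rate.* With p = 0.3 and independent items, the lower limit of 76.8% lies below 78.4%. With items moving together the rate is 70%, and 14/14 excludes it.

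**Conclusion.** The point holds as a mismatch between outcome, analysis and design. Section 2.7 supplies a patient-level rule for non-deterioration. Section 2.14 ignores it and specifies a group comparison whose coefficient and standardized difference cannot be estimated in one arm. This follows from the text and the rank of the design matrix and needs no assumption. As written, the primary analysis cannot address the primary objective.

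A reader might infer that adding a responder analysis would let the trial show that EFV slows decline. It would not. The interval at n = 14 is wide, and the untreated responder rate is unknown: 50–90% under assumed item rates of 20–50%, with the items either independent or moving fully together. Without a justified reference rate, the responder proportion describes what happened to these patients and no more.

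**What to change.** In section 2.14:

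1. Replace the group ANCOVA with the proportion of responders at week 52, by the section 2.7 rule, and its exact (Clopper-Pearson) 95% confidence interval as the primary analysis.
2. Report the individual scores as supportive within-patient changes from baseline with 95% confidence intervals, and remove the references to study groups.
3. State that, unless an untreated reference rate is justified in advance, the responder rate is descriptive and does not by itself show that EFV slows decline.
4. Optionally, if earlier scores on the same battery exist in the records, add a descriptive comparison of pre-treatment and on-treatment change, as supportive only. Tables 1 and 2 link the battery to clinical practice, but the article does not show that scores from about a year before Visit 1 exist. A formal paired test would have almost no power. An exact McNemar test needs at least 6 discordant pairs, all in one direction, for two-sided p < 0.05 (2 × 0.5^6 = 0.031). At an assumed 78% untreated rate only about 3 of 14 patients (0.22 × 14) would be pre-treatment non-responders, so the best attainable p-value is about 2 × 0.5^3 = 0.25.

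**Cost.** Items 1 to 3 use data already scheduled for collection. Changing the primary analysis is a protocol amendment, and section 2.22 sends major changes to the IRB. Section 3.1 gives the trial as still in screening in August 2022, so at that date the change could be made before any week-52 result existed. The downside is a more modest efficacy claim.
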